#### Dual-energy X-ray absorptiometry

Previous research suggests that body composition can influence cognition and brain function and may influence the mechanisms by which cognitive changes occur following acute exercise. Thus, we collect body composition measures to determine if they serve as mediator variables. Height and weight are measured and body mass index (BMI) is calculated by dividing body mass (kg) by height (m) squared. Dual-energy X-ray absorptiometry (DXA) (GE Lunar iDXA, Madison, Wisconsin) measures bone mineral content, density, and whole-body and regional soft tissue composition. Participants are instructed to wear or change into shorts and a T-shirt containing no metal. Participants lie on their back on the DXA table for about 10 min, remaining motionless with their eyes closed. The DXA can separate body mass into fat and lean measures, allowing for the evaluation of fat mass without the confounding influence of other tissues.

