#### Interventions

Children are asked not to exercise or participate in structured physical activity prior to attending any of their sessions, and this is verified via self-report before each intervention session. Maximal heart rate (HRMax) is determined from the maximal exercise test completed on day 1 and is used to determine relative exercise intensity for days 2, 3, or 4. The interventions will be completed in a randomized crossover design, such that participants will act as their own controls, through initial randomization to condition assignment and condition counterbalancing across participants. With 3 interventions, there are a total of 6 different interventions (for example, aerobic-TSST-rest, aerobic-rest-TSST, TSST-rest-aerobic, TSST-aerobic-rest, rest-aerobic-TSST, rest-TSST-aerobic). A random number generator will be used to determine which intervention order a participant receives. See Table 2 for participant timeline.

**Table 2 Tab2:** Participant timeline

Time schedule	Activity
6–30 months	Participants Enrolled
Approximately 1 week prior to intervention 1	Day 1

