#### Saliva collection (sAA and cortisol)

Salivary samples for evaluation of sAA and cortisol are collected throughout the experimental manipulation at 4 timepoints. These collection timepoints include: before cognitive testing begins/baseline, following the intervention, following post-intervention cognitive tasks, and at the completion of the visit. At each collection time, participants are seated comfortably, leaning forward with arms crossed in front of them. Unstimulated salivary samples (at least 2 mL) are collected by the passive drool technique over a 2-min period. Samples are collected into pre-weighed saliva collection tubes and immediately placed on ice. After weighing collection tubes for quantitation of saliva volume and determination of flow rate ([post-collection tube weight − pre-collection tube weight]/2 min), samples are aliquoted and frozen at − 80 °C until analysis. sAA and cortisol are packaged, shipped on dry ice, and analyzed at the University of Ottawa. sAA and cortisol are measured using commercially available kits (α-amylase Saliva Enzymatic Assay and Cortisol Saliva ELISA, IBL International, Hamburg, Germany) according to manufacturer’s instructions. Briefly, on the day of analysis, saliva samples are thawed, centrifuged at 1500×*g* for 15 min at room temperature to remove cellular contaminants and debris. For sAA, samples are diluted 1:301 in diluted sample buffer, and read in a microplate reader (POLARstar Omega, BMG Labtech, Guelph, Canada) at 22 °C at a wavelength of 405 nm at 3 and 8 min after incubation at room temperature. For CORT, samples are incubated with enzyme conjugate solution at room temperature for 2 h, washed, incubated with enzyme substrate solution at room temperature for 30 min. After the addition of the “Stop Solution” to end the enzyme/substrate reaction, samples are read in a microplate reader (POLARstar Omega, BMG Labtech, Guelph, Canada) at 450 nm within 15 min. All samples are analyzed at least in duplicate.

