### Blinding and randomization

Children are randomized after they complete the first visit. Each child receives each intervention in a counterbalanced, randomized fashion. The order of the intervention occurs through block randomization. Participants are unaware of their intervention order and are not informed of what intervention they will be completing during any given session until the actual intervention begins.

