We will investigate whether the effect of the experimental conditions (*x*) on brain function, cognition, or academic achievement (distal *y* outcomes) is mediated by sAA and CORT baseline levels (*i*) and sAA change (*s*) using a path modeling framework (Mplus v8) and conventional model-to-data fit indices [37]. Each model will be adjusted for the set of potentially confounding variables (e.g., age, sex, BMI, IQ, SES). We will interpret significant direct effects on each outcome as supporting our hypotheses. We aim to incorporate the change process of sAA (*s*) and CORT (*s*) within the same model (allowing s and s to covary). We will utilize the most current and recommended practices [38, 39] for testing moderated mediation framework that leverages the stability of the entire sample for model estimation (causal structure); 5000 bootstrap draws will be run to collect the bias-corrected bootstrapped confidence intervals (95% CI) and significant indirect effects will be decomposed in Mplus output (identical to the Sobel test [35]). If mediation is found, subsequent tests of moderation will be conducted. To test the effect of the treatment condition (i.e., exercise, TSST-C, rest) on univariate continuous outcomes (brain function, cognition, academic achievement), three separate models will be tested using planned comparisons with imposed group invariance constraints. Group comparisons in sAA mean can be simultaneously compared (Is sAA larger in exercise compared to TSST-C and/or rest?), while also comparing benefits in the continuous outcomes regressed on sAA.

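### Baseline sAA and cortisol are named as mediators of the condition effect, although they are measured before the condition is given

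*Protocol article*

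**What the plan says.** Under Power and analytic strategy, the path model is introduced with "We will investigate whether the effect of the experimental conditions" (x) on the distal outcomes (y) "is mediated by sAA and CORT baseline levels" (i), listed side by side with sAA change (s). Significant indirect effects are to be decomposed, using 5000 bootstrap draws and bias-corrected 95% intervals. Tests of moderation follow only if mediation is found.

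On timing, the saliva section gives the collection points as "before cognitive testing begins/baseline, following the intervention, following post-intervention cognitive tasks, and at the completion of the visit". Table 2 puts the baseline sample at 25–30 min and the start of every intervention at 45 min. The Days 2–4 procedure places the sample earlier still, before the EEG cap. Under Blinding and randomization, children "are not informed of what intervention they will be completing during any given session until the actual intervention begins".

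Summary of aims and Primary outcome name only the exercise-induced rise in sAA as mediator. Summary of aims treats baseline and stress-induced cortisol as something to explore in the model.

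Separately, the section on dual-energy X-ray absorptiometry says "we collect body composition measures to determine if they serve as mediator variables".

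**The concern.** A mediator has to be something that the exposure can change. A sample taken before the exposure, from a child who does not know which exposure is coming, cannot meet that condition. The plan therefore includes a path whose true value is fixed at zero by the design and would interpret a significant estimate of it as mechanism.

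This matters because mechanism is the purpose of the trial. A chance imbalance in baseline sAA or cortisol between conditions could be reported as a pathway by which exercise acts. Because moderation is tested only once mediation is found, such a result could also open that next step. Baseline has a useful role as a covariate, and the text as written does not give it that role.

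**Working it through.** **1. Time order of baseline saliva and condition**

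| Event | Time | Source |
|---|---|---|
| Baseline saliva | 25–30 min (before the EEG cap in the Days 2–4 procedure) | Table 2; Days 2–4 procedure |
| Pre-intervention cognitive tasks | 30–45 min | Table 2 |
| Child learns the condition | When the intervention begins | Blinding and randomization |
| Intervention starts | 45 min | Table 2 |

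The article is not consistent about whether the sample precedes the EEG cap, but every version puts it before the intervention.

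**2. Indirect effect**

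The indirect effect is a × b, where a is the effect of condition on the mediator and b is the effect of the mediator on the outcome given condition.

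- Through baseline: a = 0 by time order and randomised order, so a × b = 0 × b = 0 whatever b is.
- Through sAA change: the article assumes a = b = 0.39, so a × b = 0.39 × 0.39 = 0.152.

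This was checked by simulation: N = 103, two conditions per child, within-child differences, 4000 runs, baseline drawn independently of condition, and an assumed baseline–outcome effect of 0.39. The mean indirect effect was 0.000 (SD 0.041) through baseline and 0.153 (SD 0.071) through change. The change path is recovered even with baseline in the model.

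**3. How often a null baseline path would be declared significant**

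The article gives no figure for this and no value of b for baseline, so b is an assumption shown over a range. Set-up: a = 0, N = 103, continuous x, no covariates, 1,500 simulated trials, 1,000 bootstrap draws, bias-corrected 95% interval.

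| Assumed b | False mediation per test |
|---|---|
| 0 | 0.6% |
| 0.10 | 1.5% |
| 0.14 | 3.0% |
| 0.20 | 4.6% |
| 0.39 | 9.3% |

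Other runs at b = 0.39 gave about 7% to 8.6%, including 7.9% with within-child differences. Hence the range of 7–9% at that value. The simulation error at 1,500 trials is √(0.08 × 0.92 / 1500) = 0.007, or about ±1.4 percentage points at 95%, so most of the spread between runs is noise. Percentile intervals at b = 0.39 gave about 5.4–5.5%. The excess over 5% is therefore largely a property of the bias-corrected interval. These runs used fewer draws than the planned 5000, and none modelled all three conditions per child.

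**4. Body composition**

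The scan is described among the Day 1 measures. Table 2 dates Day 1 "Approximately 1 week prior to intervention 1", and "Children are randomized after they complete the first visit". One value per child applies to all three conditions, so the within-child difference between conditions is x − x = 0 and path a is exactly zero. The same section's rationale, that body composition may affect how exercise works on cognition, describes moderation. The path model lists no body composition mediator and adjusts for BMI as a confounder.

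**The case against.** The strongest defence is that i and s are the intercept and slope of a growth model. Such a model always carries the intercept, so the sentence could be shorthand for one in which baseline is already accounted for. That is plausible, and it would make the correction mostly one of wording. It does not remove the error: an intercept placed at baseline is still pre-condition, and the text says the effect is mediated by it.

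It can also be said that the main inference is untouched. This stands. The hypothesis, and the sample size calculation for mediation, concern the path from exercise through sAA to outcome. A reader might infer that the baseline path takes a spurious share of the exercise effect and so undermines that result. It does not do so on average: the baseline path averages zero and the change path is recovered.

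A third defence is that baseline might differ by condition for a real reason. Carry-over from an earlier visit, or a child guessing the remaining condition at the last visit, could produce this; the article does not discuss guessing. Neither would be a response to that day's intervention, so neither would be the mechanism under study.

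On body composition, a reader might infer that it is specified as a mediator in the analysis. The documents do not support that. It is loosely called a possible mediator in a measurement section and is absent from the mediators in the path model. Its Day 1 timing is inferred from where the section sits, as no sentence dates the scan.

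**Conclusion.** The point holds for baseline sAA and cortisol. As written, the plan tests mediation through variables that the condition cannot affect, and the true indirect effect through them is zero. This rests on three things that the article states: saliva before intervention, randomised order, and children not told the condition until it starts.

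The practical size is modest and depends on an unstated quantity. The per-test false-mediation rate runs from about 0.6% (b = 0) through 3% (b = 0.14) to 7–9% (b = 0.39). The last figure needs a medium baseline–outcome effect; the article's 0.39 is for sAA level in the powered pathway and is only borrowed here. A reader might multiply such a rate by the number of biomarkers and outcomes to predict a count of false mechanisms. The documents do not support that, because they give neither b for baseline nor a fixed number of tests, so no total should be stated.

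This is a specification error worth correcting. It does not threaten the sAA-change hypothesis. The body composition point is terminology only.

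**What to change.** In Power and analytic strategy, restate the path model so that only post-intervention change in sAA (and in cortisol, if it is kept) is a mediator. Enter same-visit baseline sAA and cortisol as covariates in both the mediator equation and the outcome equation. If the growth-model form is intended, fix the path from condition to the intercept at zero and regress the slope and the outcome on the intercept. State that the moderation step is triggered only by mediation through post-intervention change.

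In the dual-energy X-ray absorptiometry section, replace mediator with moderator, which fits both that section's rationale and the planned moderation step.

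The cost is wording and model specification. All variables are already collected, and sample size and visits do not change.

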However, minimal evidence exists regarding potential *mechanisms* underlying the transient effects of acute PA on brain and cognition. One potential mechanism involves phasic shifts in the sympathetic nervous system (SNS), as measured via the biomarker: salivary alpha-amylase (sAA). sAA is an enzyme produced by the salivary glands, which is modulated by physical and psychosocial stress as part of the first wave of the “fight or flight” response [15]. The second wave of the stress response involves the release of the glucocorticoid, cortisol from the adrenal cortex. sAA and cortisol have also been related to alterations in executive control functions (i.e., inhibition, working memory, cognitive flexibility) and academic achievement in children [16].

The SNEACY study was designed to address possible mechanisms by which acute PA acts on cognition and brain function (as measured by ERPs) in typically developing, healthy children. This lack of understanding constitutes a significant gap in the research, which is reflected in a rapid decline of PA opportunities for children throughout the school day. Thus, this study will examine the extent to which PA influences the cognitive and brain health of children. Results are expected to be particularly relevant to public health and education with potential implications for future policies aimed at improving physical and mental health during childhood. In particular, the primary goal of the SNEACY study is to discover the role of SNS activity as a mediator of the effects of a single bout of PA on brain function, cognition, and academic achievement in preadolescent children.

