### Primary outcome

The primary outcomes are changes in cognitive performance following each of the three acute interventions. Specifically, we predict that exercise-induced phasic increases in SNS activity, indicated by sAA levels, will mediate the effect of a single bout of exercise on brain function (i.e., P3 amplitude and latency), cognition (i.e., executive control), and standardized achievement test performance (i.e., mathematics, reading).

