### Power and analytic strategy

A traditional power analysis was conducted to estimate the appropriate sample size necessary for detecting a mediating effect of sAA levels on the relationship between a single bout of aerobic exercise and acute changes in cognition given the inclusion of potentially confounding variables (e.g., age, sex, BMI, IQ, SES) based on a one-sided alpha of .01 to correct for multiple outcomes and a power of 0.8. For the total effect of exercise on the ERP and cognitive outcomes, an effect size was calculated from the results reported in Hillman et al. [9], which observed increased P3 amplitude, task performance, and scholastic achievement following acute exercise relative to rest in a sample of preadolescent children resulting in a moderate-to-large effect size (Cohen’s *d* = 0.79). Therefore, assuming a medium size of Cohen’s *f*2 = 0.15 for the total effect and 8 predictors (including exercise condition, subject ID, and covariates) in the regression model, power analysis indicate that a sample size of 82 participants will provide adequate power to detect the effects of a single bout of exercise on neuroelectric function and behavioral performance. For the mediation analysis, medium effect sizes [33] were assumed for both the direct effect of exercise on sAA levels (path a: coefficient = a) and the direct effect of sAA level on the outcomes controlling for treatment condition (path b: coefficient = b). Corresponding to Cohen’s [34] criteria for medium (13% of the variance) effect size, the values of a and b were set at 0.39. Applying the Sobel [35] first-order test, the indirect effect or the mediated effect of exercise on outcomes through sAA was indicated by the product of a and b and was tested. Empirical power results [36] showed that a sample size of *N* = 103 per study was required to detect the presence of mediation. Accordingly, we aim to recruit *N* = 120 to account for attrition.

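### The only stated criterion for support is a significant direct effect, which does not match the mediation hypothesis, although a test of the indirect effect is also planned

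*Protocol article*

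**What the plan says.** The hypothesis is mediation. The Background gives the primary goal as to "discover the role of SNS activity as a mediator of the effects of a single bout of PA on brain function". The Primary outcome section predicts that "exercise-induced phasic increases in SNS activity, indicated by sAA levels, will mediate the effect of a single bout of exercise on brain function", and extends this to cognition and achievement. The Summary of aims states the same hypothesis.

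The first paragraph of Power and analytic strategy sizes the trial on that quantity: "the indirect effect or the mediated effect of exercise on outcomes through sAA was indicated by the product of a and b". It uses the term direct effect twice, once for exercise on sAA (path a) and once for sAA on the outcomes with condition held fixed (path b).

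The second paragraph sets up a path model to ask whether the condition effect is mediated. It then gives the criterion: "We will interpret significant direct effects on each outcome as supporting our hypotheses". Further on it plans 5000 bootstrap draws with bias-corrected 95% intervals, says that significant indirect effects will be decomposed, and makes tests of moderation conditional on finding mediation. It does not say that a significant indirect effect is what supports the hypothesis.

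**The concern.** A mediation hypothesis is a statement about a×b: exercise moves sAA (a), and sAA moves the outcome (b). The sentence on support names a different parameter.

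- **Direct effect as c'.** This is the usual meaning in a mediation model: the part of the condition effect that does not pass through sAA. A large c' is no evidence for the sAA mechanism, and complete mediation implies c' = 0.
- **Direct effect as path b.** This is one of the two paths. If exercise does not change sAA, a significant b does not show mediation.
- **Hypotheses as the predicted exercise benefit** (first aim and Discussion). The matching quantity is the total effect of condition, not an effect adjusted for sAA.

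The paragraph therefore leaves two routes to a positive statement about mechanism, for P3 amplitude and latency, executive control, mathematics and reading. Someone following the text literally could report a significant direct effect as support for the sAA mechanism while the interval for a×b includes zero.

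**Working it through.** **Inputs from the protocol** (Power and analytic strategy): a and b ("the values of a and b were set at 0.39"); level and power ("based on a one-sided alpha of .01 to correct for multiple outcomes and a power of 0.8"); sizing test ("Applying the Sobel [35] first-order test"); N = 103, with 120 to be recruited to allow for attrition.

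**Assumptions.** The protocol gives no value for c'. I take 0 (complete mediation) and 0.39 (its own medium value for a and b). X and both residuals have unit variance, so path a explains 0.39²/(1 + 0.39²) = 0.1521/1.1521 = 13% of variance, as the protocol states. There is one observation per child and there are no covariates.

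**1. The plan's own figure.** Here SE(a) = SE(b) = 1/√N, so the Sobel statistic has mean ab√N/√(a² + b²) = 0.1521√N/0.5515 = 0.2758√N.

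- One-sided 0.01, power 0.80: N = ((2.326 + 0.842)/0.2758)² ≈ 132. Simulation gives about 115.
- Power at N = 103: Φ(0.2758 × 10.149 − 2.326) = Φ(0.47) = 0.68. Simulation gives 0.71.
- Two-sided 0.05: N = ((1.960 + 0.842)/0.2758)² ≈ 104.

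So 103 does not follow from the stated level, though it lies close to the result for two-sided 0.05. The present point does not depend on this.

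**2. How often each rule declares support.** Model: M = aX + e₁ and Y = bM + c'X + e₂, with 40,000 simulated trials per row, N = 103, one-sided 0.01.

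| Truth | Mediation | c' significant | b significant | Sobel a×b significant |
|---|---|---|---|---|
| a = b = 0, c' = 0.39 | none | 0.93 | 0.01 | 0.000 |
| a = 0.39, b = 0, c' = 0.39 | none | 0.89 | 0.01 | 0.0026 |
| a = 0, b = 0.39, c' = 0 | none | 0.01 | 0.93 | 0.0025 |
| a = b = 0.39, c' = 0 | complete | 0.01 | 0.93 | 0.71 |

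**3. Check by hand.** With a = 0, c'√N = 0.39 × 10.149 = 3.96, so power is about Φ(3.96 − 2.326) = 0.95. With a = 0.39, the variance of X given M is 1/1.1521 = 0.868, so the mean is 3.96 × √0.868 = 3.69 and power is about Φ(1.36) = 0.91. These normal approximations lie slightly above the simulated 0.93 and 0.89, which use t critical values and estimated variances. The figure for b with a = 0 follows from the same arithmetic.

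**4. Sensitivity.**

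- Two-sided 0.05 (the level of the planned interval), N = 103: the c' rule gives 0.97 and 0.95 in the first two rows and 0.05 under complete mediation. The b rule gives 0.97 in the third row. Sobel gives 0.88 under complete mediation.
- N = 120, one-sided 0.01: the c' rule gives 0.96, 0.94 and 0.01. The b rule gives 0.96 in the third row. Sobel gives 0.83 under complete mediation.

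The value 0.39 for c' sets the size but not the pattern. When a×b = 0, false support on the c' reading equals the power for c'. When c' = 0, that rule fires at alpha by construction.

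**The case against.** The strongest reply is that the right test is already in the plan. The same paragraph asks whether the effect is mediated, plans bootstrap intervals, refers to significant indirect effects and conditions moderation on mediation being found. The trial is sized on a×b. This stands: no mediation test is missing, and a reader who inferred that the mechanism conclusion rests wholly on the wrong parameter would go further than the text.

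Second, the protocol otherwise uses direct effect only for paths a and b, never for c'. Effects on each outcome then fits path b best. This also stands, and it limits the point. A reader might infer that the rule both confirms mediation that is absent and misses mediation that is complete. The second half holds only if c' is meant. On the path b reading, complete mediation is detected in about 0.93 of trials, and the first two rows of the table give support only at about 0.01. What remains on that reading is false support when a = 0. The planned comparison of mean sAA between conditions would bear on path a, but the support sentence does not require it.

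Third, hypotheses is plural and may cover the predicted benefit of exercise. Where b = 0 and c' = 0.39, exercise does help, so that prediction would be true. Even so, the total effect is the quantity that answers it.

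Finally, a fuller analysis plan may exist. That would matter if the criterion had been left out. Here it is stated, and stated wrongly.

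**Conclusion.** The sentence is wrong as written. It is the only stated criterion for support, and neither c' nor path b, nor the exercise-benefit reading, makes it match the mediation hypothesis or the a×b used for sizing. At N = 103 and one-sided 0.01:

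- **c' reading:** support in about 0.89 to 0.93 of trials without mediation if c' = 0.39 (assumed), and in about 0.01 under complete mediation.
- **Path b reading:** no failure under complete mediation, but support in about 0.93 of trials when a = 0 and b = 0.39.

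The figures are illustrative. They use a continuous X, one independent observation per child and no covariates, not the three-condition crossover. The mismatch between criterion and hypothesis does not depend on them. The documents support a finding of a wrong criterion placed beside a suitable planned test, and no more than that.

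**What to change.** Replace the sentence in Power and analytic strategy with:

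> The mediation hypothesis is supported for an outcome only if the planned bootstrap confidence interval for the indirect effect of exercise versus rest through change in sAA (a×b) excludes zero in the predicted direction. The exercise benefit (Aim 1) is judged by the total effect of condition. The direct effect is reported as the part not explained by sAA.

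The condition for the moderation tests should refer to the same criterion. The edit should also name the level of the interval, because the one-sided 0.01 used for sizing and the planned 95% interval are not the same level; that is a separate matter to reconcile.

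The cost is a few lines of wording. No extra data, visits or analyses are needed, since the bootstrap is already planned.

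### The trial is sized at one-sided .01 to correct for multiple outcomes, but the only criterion given for a significant indirect effect is a 95% interval, so on the natural reading the correction is not carried into the mediation analysis

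*Protocol article*

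**What the plan says.** Both statements stand in the protocol article, section Power and analytic strategy.

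- **Sizing paragraph.** The power calculation for mediation is "based on a one-sided alpha of .01 to correct for multiple outcomes and a power of 0.8". For the mediation paths, "the values of a and b were set at 0.39". The test is the Sobel "first-order test, the indirect effect or the mediated effect of exercise on outcomes through sAA was indicated by the product of a and b", and the result is that N = "103 per study was required to detect the presence of mediation". For the total effect, with f² = "0.15 for the total effect and 8 predictors", the paragraph says that "a sample size of 82 participants will provide adequate power".
- **Analysis paragraph.** For the indirect effects, "5000 bootstrap draws will be run to collect the bias-corrected bootstrapped confidence intervals (95% CI". Indirect effects found significant are then decomposed, and moderation is tested only if mediation is found. No other significance level, interval level or multiplicity procedure appears there or elsewhere in the article.

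Primary outcome applies the sAA mediation hypothesis to P3 amplitude, P3 latency, executive control, mathematics and reading.

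**The concern.** The plan recognises that it tests several outcomes and states a stricter level to deal with this. That level protects against false positives only if it is also used to decide which indirect effects are significant. The analysis paragraph instead names the conventional interval, which carries no correction.

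Mediation by sAA is the trial's stated primary goal, so the conflict bears on its main claim. A reader of the results would assume the error rate in the sizing paragraph, while the analysis as written would deliver a larger one. The same finding also decides whether moderation is tested. This is not a detail that the article leaves to a longer document: it states both levels, and an analysis plan could follow one as the decision level only by departing from the other.

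**Working it through.** **Inputs.** From Power and analytic strategy: alpha .01 one-sided, power 0.80, a = b = 0.39, Sobel test, N = 103; f² = 0.15, 8 predictors, N = 82; 95% bias-corrected bootstrap interval. From Primary outcome: five named outcomes. Assumptions: these five form the family, and they are independent.

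**1. The plan's own sample sizes.**

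| Calculation | Level | Result |
|---|---|---|
| Sobel, simulated, total variances 1 | one-sided .01 | power 0.776 (normal X) to 0.788 (binary X) at N = 103; 0.80 reached at about 105–106 |
| Same | two-sided .01 | power 0.631 to 0.638 at N = 103 |
| Sobel, simulated, unit residual variances | one-sided .01 | N about 114–115 |
| Sobel, closed form | one-sided .01 | N = 122 to 132 |
| Sobel, closed form | two-sided .05 | N = 96 to 104 |
| Total effect, 1 tested of 8 predictors | two-sided .01 | N = 82 (power 0.803) |
| Total effect, same | one-sided .01 | N = 70 |

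N = 103 comes within 3% of the simulated Sobel result at one-sided .01. It also falls in the closed-form range at two-sided .05, so the figure alone does not show which level was used. N = 82 matches two-sided .01. The point therefore rests on the stated .01, and its sidedness is unclear.

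**2. Interval level that matches the stated alpha.**
- One-sided .01: 1 − 2 × .01 = .98, a 98% interval.
- Two-sided .01: 1 − .01 = .99, a 99% interval.
- A 95% interval leaves (1 − .95)/2 = .025 per tail. Against one-sided .01 the ratio is .025/.01 = 2.5.

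**3. Chance of at least one false positive in the predicted direction**, 1 − (1 − α)^k for k independent outcomes:
- k = 5, α = .025: 1 − .975^5 = 0.119
- k = 5, α = .01: 1 − .99^5 = 0.049
- k from 3 to 8: 7.3% to 18.3% at .025, against 3.0% to 7.7% at .01

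**4. A separate matter: how the bootstrap interval behaves.** A simple mediation model was simulated at N = 103, with one exposure per subject, no covariates and no crossover structure. Over several runs (1,000 to 2,000 bootstrap draws per data set):

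| Interval | Rejection per tail, a = 0.39, b = 0 | Power, a = b = 0.39 |
|---|---|---|
| Bias-corrected 95% | about 3.5–5% | 0.96 |
| Bias-corrected 98% | about 2% | about 0.91 |
| Percentile 98% | about 1.2% | about 0.88 |

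The null with path a present is the relevant one, because the Discussion expects sAA to rise with exercise whether or not it matters for cognition. With both paths zero, the bias-corrected 95% interval lay above zero in only 0.3% of data sets.

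**The case against.** The decision rule is inferred. The analysis paragraph never says that mediation is declared when the interval excludes zero, and the same sentence likens the decomposed effects to the Sobel test, which the sizing paragraph places under .01. A 95% interval can be reported beside a test at a stricter level, and a separate analysis plan may say so. This stands as a limit: the fair statement is that the only level given in the analysis conflicts with the sizing level. It does not remove the conflict, because nothing in the article carries .01 forward.

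A reader might infer a roughly fourfold inflation, or a family-wise error near 20% (at 4.2% per tail, 1 − .958^5 = 0.193). The documents do not support that as the size of the contradiction. It adds the bootstrap's own excess to the mismatch of levels, assumes independence among outcomes measured on the same children, and relies on a model without the crossover or covariates. With residual correlation of 0.5 the simulated figure was about 14%.

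A reader might also take it as given that .01 was chosen to cover exactly five outcomes, or that the planned condition comparisons share the fault. The sizing paragraph gives no number of outcomes; five comes from Primary outcome. For the planned comparisons no level is stated, which is silence that an analysis plan may fill and not a contradiction.

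**Conclusion.** The concern holds as an inconsistency between two paragraphs of one section. On the natural reading, the analysis tests each indirect effect at a nominal .025 in the predicted direction where the plan states .01, a factor of 2.5 that needs no simulation. The family-wise comparison depends on the assumed five-outcome family and on independence. If .01 was meant two-sided, 95% is still too lenient. The bootstrap's excess is a secondary point about method, illustrated only in a simplified model; it bears on the choice of interval, not on whether the two levels conflict. Data collection is unaffected, and the conflict can be settled before analysis.

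**What to change.** - In the analysis paragraph of Power and analytic strategy, state that an indirect effect is declared only if the bootstrap interval at the planned level excludes zero in the hypothesised direction: 98% for one-sided .01, or 99% if .01 was meant two-sided. Keep the 95% interval as descriptive.
- In the sizing paragraph, clarify the sidedness of .01, since N = 82 reproduces at two-sided .01 and N = 103 fits one-sided .01 better. This has to come before the interval level is fixed.
- Prefer a percentile interval, because aligning the level alone leaves the bias-corrected 98% interval at about 2% per tail. This is a change of method beyond reconciling the levels and should be given its own reason in the text.

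The cost is a few lines of wording and slightly wider intervals. No extra participants are needed for 98% intervals under the plan's own effect sizes in the simplified model. Bootstrap power at 99% was not computed and should be checked if the two-sided reading is chosen.
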